### Selection of the population and allocation of the intervention

2.6.

The implementation research has been conducted in all woredas of the Gedeo Zone. Study woredas have been treated as clusters, with an equal number allocated to both intervention and non-intervention arms. Matched peer random allocation has been employed. To reduce subjective allocation, matching has been performed based on the performance level of the woredas (based on key indicators) and distance. The woredas have also been classified as urban and rural areas, and six intervention and six comparison arm woredas have been randomly selected in collaboration with the zonal health department. To avoid information contamination between the intervention and control arms, a buffer zone has been created based on the distance within the districts. Finally, all health management staff have been included in the selected woredas (Figure 1).

**Figure 1 F1:**
[figure not shown]
Sampling procedure on improving data use in decision-making and maternal healthcare service utilization through DIPH approach in districts, Gedeo Zone, southern Ethiopia, 2022.

#### Embedding

2.6.1.

The DIPH approach has been provided as a package and integrated into the current decision-making platform of the districts [such as Performance Review Team (PRT) meetings], adding a formal and structured coordination process between various departments and data sharing for evidence-based decision-making, planning, and resource allocation in accordance with local health priorities. The PRT, sometimes called the Performance Monitoring Team (PMT), which is a multidisciplinary team primarily responsible for improving data quality and using information regularly to evaluate progress and enhance healthcare delivery, is the main platform for routine data use in the health sector. In Ethiopia, the PRT or PMT is led by the head of the facility. Department leaders and/or case team leaders serve as members of the HMIS office, which acts as a secretary. The PRT meetings of the woreda health management have been used as a platform to introduce the DIPH packages.

Activities have been primarily focused on
•encouraging the regular analysis and use of available data to comprehend woreda-level health system improvement.•strengthening the PRT forum to engage all government and non-governmental stakeholders in identifying challenges and solutions, as well as assessing resource allocation and responsibilities. These meetings have been convened with the aim of consensus building and collective decision-making to improve health systems and services in their areas.

### Blinding

2.7.

•The nature of the interventions has been designed for implementation by management health workers. As a result, it cannot mask program implementers and health workers. However, during implementation, baseline, and endpoint data collection, all study participants and data collectors would be kept in the blind about the research question and hypothesis that the team came up with.

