#### Preparatory phase

2.8.2.

*Prepare materials***.** Logistics, including job aids such as guidelines, has been prepared before the implementation.

*Organizing the DIPH field team*. The researcher team, also referred to as the implementation support team, has consisted of six members, including one health professional each from health service management, health informatics, reproductive health, epidemiology, and biostatistics and one health management staff from the zonal health department as a coordinator, supervisor, and data manager. To facilitate the overall activities, the principal investigator of the research is responsible. The field team has the following roles: prepare and develop data collection tools, provide training to health professionals, and conduct monthly supportive supervision using a performance checklist in line with the health facility PRT. The teams will acquire and examine data from six district health offices, which are DIPH-implementing districts, and six control districts that will not be participating in DIPH. According to the priority areas determined by the district health offices, the PRT evaluates monthly progress toward a set of indicators.

The assistance provided by the DIPH team, which consists of action plan preparation, follow-up, and supportive supervision, benefits the team leaders of the district health office. As the purpose of the DIPH is to strengthen decision-making, unit leaders of district health offices are working with the DIPH field team to gain a clearer understanding of their data and make better use of it.

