### Data collection tools and procedures

2.10.

A pre-tested interviewer-administered structured questionnaire, based on the Performance of Routine Information System Management tools (version 3) (30) and adapted to the local context, has been used to improve data use in decision-making and utilization of maternal healthcare services through the DIPH approach in districts of the Gedeo Zone, southern Ethiopia, 2022. The questionnaire has two broad categories, namely, data use in decision-making and utilization of maternal healthcare service. It will be organized in an English version and then translated into local languages (Gedeuffa and Amharic) and finally retranslated into an English version to ensure consistency. The collection of baseline data has been carried out by the organized field teams. For end-line survey data collection, an independent team of four data collectors and one supervisor has been recruited for 1 month.

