### Ethical consideration

2.13.

An ethical approval letter was obtained from the Institutional Review Board of Dilla University (Ref. No.: duchm/irb/026/2023), and an official letter of cooperation request (Ref. No.: 1000/206/15) was submitted to the respected health facilities. After discussing and explaining the purpose and whole course of the study, written informed consent has been obtained from each health administrative staff member just before the actual data collection. Confidentiality has been assured at all stages of the study by making the questionnaire anonymous. Participant involvement has been voluntary, and those who have been unwilling and needed to quit their participation in the interim have been informed of their right to do so.

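### Section 2.7 claims blinding that 2.13 contradicts for participants and 2.8.2 with 2.10 contradict for baseline collectors; only the end-line team could be blind, and it is promised blindness to the hypothesis, not to allocation

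*Protocol article*

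**What the plan says.** Section 2.7 (Blinding) first concedes that, for this kind of intervention, "it cannot mask program implementers and health workers". It then claims a narrower safeguard for implementation, baseline and end line: "all study participants and data collectors would be kept in the blind about the research question and hypothesis". Knowledge of which woredas are in which arm is not mentioned.

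Section 2.13 (Ethical consideration) describes consent, taken immediately before data collection: "After discussing and explaining the purpose and whole course of the study, written informed consent has been obtained from each health administrative staff member".

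Section 2.10 (Data collection tools and procedures) says of baseline: "The collection of baseline data has been carried out by the organized field teams". For end line it recruits a separate independent team of four collectors and one supervisor.

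Section 2.8.2 (Preparatory phase) identifies the field team: "The researcher team, also referred to as the implementation support team, has consisted of six members". Its tasks are to "prepare and develop data collection tools, provide training to health professionals, and conduct monthly supportive supervision".

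Section 2.12 (Data management) tests differences within and between groups, and takes the net effect as the difference between the arms' changes from baseline to end line.

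**The concern.** Both outcomes depend on what staff tell an interviewer. Under 2.9, data use is built from 20 yes/no items and rated good only if every answer is yes; maternal service use is a provider report in percent. With such outcomes a reader will look to the blinding section when judging assessment bias. That section offers a safeguard which other sections show is absent for participants and for baseline collectors.

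The safeguard also points at the wrong knowledge. What mainly protects scoring is that the assessor does not know the arm. An end-line interviewer who has never heard the hypothesis, but knows that a woreda received DIPH training and monthly support, can still score it more generously.

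The Introduction itself names staff awareness of being evaluated as a rival explanation that the comparison group should exclude. A control arm does that only if awareness is equal in both arms. Here only intervention woredas are trained and supported (2.8.3).

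**Working it through.** **The passages side by side**

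| Group | Claim in 2.7 | What other sections say | Result |
|---|---|---|---|
| Participants | Blind to question and hypothesis | 2.13: purpose and full course explained to each; 2.8.3: DIPH staff trained for 5 days on the strategy | Contradicted |
| Baseline collectors | Same | 2.10: field teams; 2.8.2: the field team is the research and implementation support team | Contradicted; 2.7 attributes the hypothesis to this same team |
| End-line collectors | Same | 2.10: independent team | Not contradicted; allocation not addressed |

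The research questions in 1.2 are simply the effect of DIPH on each of the two outcomes. Explaining the study's purpose therefore discloses them.

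**How scoring error reaches the net effect**

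Write e for the average scoring error in percentage points, with I and C for the intervention and control arms and 0 and 1 for baseline and end line.

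- Net effect in 2.12: (I1 − I0) − (C1 − C0).
- Bias = (eI1 − eC1) − (eI0 − eC0).
- If the baseline team errs equally in both arms, eI0 − eC0 = 0 and nothing is left. If it errs differently, the whole difference passes through, because baseline is subtracted at full weight.
- If the end-line contrast is instead adjusted for baseline with slope β, the baseline part becomes −β(eI0 − eC0). At β = 1 this equals the difference-in-differences; at β = 0 it vanishes.
- Within-arm change carries e1 − e0. Two different teams produce e1 and e0, so a change of assessor does not cancel inside one arm.

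**Size for the data-use outcome**

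Inputs: 60 staff per arm and a planned difference of 25 points (2.5). The plan gives no figure for scoring error, so there is none to reproduce.

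- One reclassified person: 1/60 = 1.7 points.
- Net between-arm imbalance of 0, 3 or 6 staff (assumed): 0, 3/60 = 5, or 6/60 = 10 points.
- Against 25 points: 0%, 5/25 = 20%, or 10/25 = 40%.

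It is the net imbalance that counts. Equal numbers reclassified in the same direction in both arms give zero.

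**Is an imbalance of that order far-fetched?**

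Assume 20 independent items and take the plan's 50% as the share rated good. The per-item yes rate is then q = 0.5^(1/20) = 0.966. Shift q in one arm at one time point:

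| Shift in per-item rate | Share rated good | Change (points) |
|---|---|---|
| −1 point | 40.6% | −9.4 |
| −0.5 point | 45.1% | −4.9 |
| +0.5 point | 55.4% | +5.4 |
| +1 point | 61.4% | +11.4 |

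The all-yes rule thus magnifies small scoring differences. Real items will be correlated, so this shows the mechanism and is not an estimate. It does not apply to maternal service use, which is not scored by that rule.

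**The case against.** The strongest reply is that difference-in-differences removes any baseline scoring error common to both arms. For the error to differ by arm, baseline collectors must have known or guessed the allocation, and no section says they did. This stands. Section 2.8.3 has study districts selected at the training workshop, and 2.6 has the zonal health department, which supplies a field-team member (2.8.2), collaborating in the random selection. Knowledge of allocation is therefore possible, but the timing of allocation relative to baseline collection is not given.

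Second, the identity of the baseline collectors is not beyond doubt. Section 2.11 gives data collectors and the supervisor 5 days of training in basic technique, which fits awkwardly with researchers who wrote the tools. That training can, however, be read as meant for the recruited end-line team. No field team other than the one in 2.8.2 is described.

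Third, 2.7 never claims blinding to allocation, and how interviewers are briefed is detail that an article may leave to a fuller document. This is fair: silence on allocation is not a false statement. It matters because the safeguard that is stated does not do the work a reader would credit it with.

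Fourth, masking interviewers does not reach the firmer route to bias, which is trained, unmasked staff reporting on their own data use at end line. That also stands, and limits what the fix can achieve.

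A reader might go further and infer that the trial has no blinding at all, or that unblinded scoring has entered the net effect. The document supports neither. Nothing contradicts hypothesis-blindness for the end-line team, and arm-specific scoring is a possibility that the text leaves open.

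**Conclusion.** The contradiction is established from the text: 2.7 cannot be true for participants, nor for baseline collectors on the plain reading of 2.8.2 with 2.10. Only the end-line team could be blind, and then to the hypothesis rather than to the arm.

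The consequence for the estimate is conditional. Arm-specific scoring can bias the net effect; the document neither shows nor excludes it. The illustrative range for data use is 0 to 10 points, or 0% to 40% of the planned 25. It rests on an assumed net imbalance of 0 to 6 of 60 staff, and zero is a legitimate value. The direction is open: stricter baseline scoring of intervention woredas would inflate the net effect, and more lenient scoring would shrink it. No size can be given for maternal service use.

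This should be corrected because it misstates a safeguard and the remedy is cheap. It does not show that the result is wrong.

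**What to change.** 1. Rewrite 2.7 to say that participants, implementers and baseline collectors are not blinded, and to state separately what the end-line team is and is not told.
2. Require that the end-line team already recruited takes no part in DIPH training, support or supervision and is not told woreda allocation. If collection is already complete, report what the team knew.
3. Base the effect on the between-arm contrast at end line, measured by that one team and adjusted for the woreda baseline rather than subtracting it at full weight.
4. Do not use within-arm before/after tests as evidence of effect, since they compare two assessor teams. Within-arm changes may still be described.
5. State self-report by unmasked intervention staff as a remaining limitation.

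Cost: protocol wording, a briefing rule and a change to the analysis, with no extra staff. Adjustment uses one degree of freedom. With 12 woredas and two arms, 12 − 2 = 10 falls to 9; if the matching in 2.6 forms six pairs that are kept in the analysis, 6 − 1 = 5 falls to 4. Adjustment still uses the baseline measurement, so it reduces the influence of any arm-specific baseline error without necessarily removing it. Some interviews will reveal the arm, so end-line masking will be partial.

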### Phases of the implementation

2.8.

The study has four core phases, such as the orientation phase, preparatory phase, intervention phase, and monitoring and evaluation phase.

#### Orientation/discussion phase

2.8.1.

*Policy dialog*. Before commencing implementation, including its training phase, a detailed discussion has been conducted with responsible bodies on the potential implementation of the strategies in the zone. Stakeholders include the zonal health department, program managers, technical experts, and non-governmental organizations; finally, a consensus has been achieved among them.

#### Preparatory phase

2.8.2.

*Prepare materials***.** Logistics, including job aids such as guidelines, has been prepared before the implementation.

*Organizing the DIPH field team*. The researcher team, also referred to as the implementation support team, has consisted of six members, including one health professional each from health service management, health informatics, reproductive health, epidemiology, and biostatistics and one health management staff from the zonal health department as a coordinator, supervisor, and data manager. To facilitate the overall activities, the principal investigator of the research is responsible. The field team has the following roles: prepare and develop data collection tools, provide training to health professionals, and conduct monthly supportive supervision using a performance checklist in line with the health facility PRT. The teams will acquire and examine data from six district health offices, which are DIPH-implementing districts, and six control districts that will not be participating in DIPH. According to the priority areas determined by the district health offices, the PRT evaluates monthly progress toward a set of indicators.

The assistance provided by the DIPH team, which consists of action plan preparation, follow-up, and supportive supervision, benefits the team leaders of the district health office. As the purpose of the DIPH is to strengthen decision-making, unit leaders of district health offices are working with the DIPH field team to gain a clearer understanding of their data and make better use of it.

#### Implementation/intervention phase

2.8.3.

*Training*. Before initiating the first DIPH cycle, the district health management staff of DIPH woredas has been provided 5 days of intensive training based on the designed curriculum in their zonal city. On average, 10 health administrative staff per woreda have received training from the research team. The training also involves experts from the zonal health department, in addition to the head of the health department of woredas, program officers, and an HMIS focal person. The DIPH research investigator team has prepared the 5-day residential training. DIPH-related issues, including the strategy concept, training guidelines, and other evidence, have been clearly discussed with each stakeholder during the workshop. Then, readjustment has been performed in accordance with the discussion and recommendations raised by the workshop participants, and the study areas/districts have been selected together with those invited participants.

*Technical support*. Those woreda health managers will benefit from the organized implementation support team throughout the intervention. The intervention will focus on five basic steps of DIPH (assess, engage, define, plan, and follow-up). This strategy enabled the health management staff to assess the situations based on the available data, engage stakeholders, prioritize the identified problems, and prepare a clear monthly action plan and follow-up.

#### Monitoring and evaluation phase

2.8.4.

1.To ensure the quality of the intervention provided and data collected, the research team and other stakeholders have had frequent meetings to share progress, best practices, challenges, and possible solutions to overcome barriers to the implementation.2.Monitoring and evaluation of the intervention activity have been assessed from the beginning to the end of the intervention. Both qualitative and quantitative methods have been used in the evaluation. Depending on the findings of each monitoring and evaluation, necessary modifications and adjustments have been made to the intervention progress. We have used formative and summative evaluation during and following the initiation of the intervention.3.The performance of the DIPH strategy has been reviewed and evaluated during monthly supervision and quarterly meetings, at which point necessary feedback has been given. The parameters for this assessment will be the number of Performance Monitoring Team meetings conducted, problems identified and prioritized, action plans prepared, and monitoring and evaluations conducted. In addition, potential obstacles/barriers have been identified and discussed during the meeting. Woredas with better performance have been appreciated and recognized, and their experience has been shared with other woredas for better implementation results.4.Finally, the intervention effect on data use in decision-making and utilization of maternal healthcare services has been assessed at the end.

### Operational definition

2.9.

**The DIPH approach** is a structured decision-support approach in promoting the use of locally available data for health decision-making at the woreda level (7).

**Data use in decision-making** is a process through which district health managers, decision-makers, and stakeholders explicitly consider the information in gap identification, prioritization, root cause analysis, action plan development, and follow-up. The five components of the outcome variable were identifying indicators in the department, calculating targets vs. achievements, providing feedback to health workers at the lower levels, calculating program coverage, and evidence showing the use of data to notify decisions. It has been measured by computing 20 yes/no questions and said to be good if all the responses are yes unless poor (30, 31).

**Maternal health service utilization** is the overall utilization of common maternal healthcare services such as antenatal care, delivery, postnatal care, and family planning from a provider standpoint (report) in percent. It has been measured using 10 core indicators, each at 100% (21, 32).

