In low-resource countries such as Ethiopia, the utilization of local data for health system planning and decision-making is frequently constrained (7). The HMIS generates huge amounts of data regarding health service delivery and population health, enabling decentralized health systems to make data-driven decisions. Health facilities are trying to utilize local data available in health sectors (health post, health center, and hospital), such as daily, weekly, monthly, quarterly, and annually reported services and diseases, as well as data from other sectors such as nutrition, water, and sanitation, and other data directly related to the improvement of maternal health services (4). However, the data are rarely used locally (5). In practice, HMIS data are underutilized at the community and district levels because there is no defined process for their utilization, or they may be unavailable, incomplete, or of poor quality (8, 9).

Improving health information systems will initially result in improved outputs of higher quality and timely data. Then, data must be utilized to improve the functioning of the five other building blocks of the health system, namely, health services, the workforce, medical supplies, financing, and leadership to finally affect service delivery and health outcomes. However, data are frequently insufficiently utilized in program creation and improvement, policy formulation, strategic planning, or advocacy and instead sit on reports, shelves, or databases (8).

According to the literature, the overall level of routine data or health information used for decision-making among health workers working in health institutions is insufficient and varies by country and region of the world. In some African countries other than Ethiopia, it runs from 38% in Côte d'Ivoire to 69.6% in Kenya (10–14). The result of a systematic review in Ethiopia revealed that the overall utilization of data among care providers was 57.42% (15), which ranges from 45.8% in the East Gojjam Zone to 78.5% in North Gondar (16–20).

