### Study participants

2.3.

The study participants have been the head of the health department, all program officers, and data managers at the woreda level. All eligible woreda staff have been interviewed. We have anticipated that 10 eligible staff members will be available in each woreda, and we have intended to include all of them in the study.

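### Utilisation is a provider-side report, and DIPH could change reporting in one arm only; the difference-in-differences would keep that change, so the result supports a claim about reported utilisation

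*Protocol article*

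**What the plan says.** All references are to the protocol article.

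- **Outcome.** Sections 1.1 and 1.2 ask whether DIPH improves utilisation of antenatal care, delivery, postnatal care and family planning. Section 2.9 measures this as use of "antenatal care, delivery, postnatal care, and family planning from a provider standpoint (report) in percent". It adds: "It has been measured using 10 core indicators, each at 100" percent.
- **Source.** Section 2.10 describes one interviewer-administered instrument for both outcomes: "The questionnaire has two broad categories, namely, data use in decision-making and utilization of maternal healthcare service". Section 2.3 names the respondents: "The study participants have been the head of the health department, all program officers, and data managers at the woreda level". No survey of women and no recount of registers is described for this outcome.
- **Intervention.** Section 2.8.3, on the DIPH woredas: "On average, 10 health administrative staff per woreda have received training from the research team". Section 2.6.1 embeds the package in the PRT, "which is a multidisciplinary team primarily responsible for improving data quality and using information regularly to evaluate progress", and lists strengthening that forum among the activities. According to the abstract, control staff carry on with their usual work.
- **State of the data.** The Introduction, explaining why HMIS data are underused locally, says that no process for using them is defined, "or they may be unavailable, incomplete, or of poor quality".
- **Analysis.** Section 2.12 subtracts the control arm's change from the DIPH arm's change, because some change would occur over time without DIPH.

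**The concern.** The people who supply the utilisation figures in the intervention arm are the people the intervention trains and supports. The platform it strengthens has data quality among its main tasks. If reporting becomes fuller or more accurate in six woredas and not in the other six, the measure has changed in one arm only.

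A positive net effect could then mean that more women were served, or that the same services were reported more completely. If DIPH instead corrects over-reporting, a real gain could be hidden. As written, the plan has nothing to separate these explanations, yet the objective and the outcome are worded as utilisation itself.

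**Working it through.** The plan gives no figure for reporting completeness, so there is none to reproduce. The check has two parts.

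**1. Does the planned estimator remove a reporting change in one arm?**

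Let U be true utilisation and r the reporting ratio (reported divided by true, with the denominator unaffected). Reported utilisation is U × r. With U the same in both arms and at both times, the section 2.12 estimate is

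DiD = U × [(r_end − r_base) in DIPH − (r_end − r_base) in control].

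- If r changes equally in both arms, the bracket is 0 and the estimate is 0. This is the common change over time that section 2.12 has in mind.
- If r changes in the DIPH arm only, the control term is 0 and the whole of U × (r_end − r_base) remains.

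**2. How large could it be?**

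Inputs:
- U = 50%, taken from the expected baseline level in section 2.5 and held flat.
- Planned difference of 25 percentage points (section 2.5), used only as a yardstick.
- Completeness values: assumptions, since the document gives none.

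| | Baseline | End line | Change |
|---|---|---|---|
| Control, completeness 80% throughout | 0.50 × 0.80 = 40% | 0.50 × 0.80 = 40% | 0 |
| DIPH, 80% to 90% | 0.50 × 0.80 = 40% | 0.50 × 0.90 = 45% | +5 points |
| DIPH, 80% to 95% | 0.50 × 0.80 = 40% | 0.50 × 0.95 = 47.5% | +7.5 points |

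The spurious net effect is +5 to +7.5 points, which is 5/25 = 20% to 7.5/25 = 30% of the planned difference, with no extra woman served.

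This example starts at 40% reported, whereas section 2.5 may mean 50% as the reported baseline. Fixing the reported baseline at 50% gives DiD = 50 × (r_end / r_base − 1):

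- 0.90 to 1.00: +5.6 points
- 0.80 to 0.90: +6.2 points
- 0.70 to 0.90: +14.3 points
- 0.60 to 0.90: +25.0 points, equal to the whole planned difference

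The sign can turn. If the reporting ratio fell by 0.10 in the DIPH arm because over-reporting was corrected, the shift would be 0.50 × (−0.10) = −5 points.

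**The case against.** The strongest reply is that the evidence for a reporting change is indirect, and much of this stands.

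- **DIPH is not described as a reporting intervention.** Its steps are to assess, engage, define, plan and follow up, and section 2.9 defines it as promoting use of available data. No component for completing or correcting reports is stated. This stands: the effect on reporting is an inference.
- **The PRT is not unique to the DIPH arm.** It is the existing platform, and nothing says that control woredas lack it. This stands too. What differs by arm is the training, the support and the strengthening of the forum.
- **The remark on incomplete HMIS data is general background.** It gives no estimate for Gedeo. It shows only that the protocol's own account leaves room for reporting to change.
- **The outcome is already labelled as a provider report.** That is true in section 2.9, but the objective, the outcome list and the research questions drop the qualifier.

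Two safeguards do not answer the point. The independent end-line team (section 2.10) and blinding to the hypothesis (section 2.7) leave the figures coming from the trained staff. The checks in section 2.11 concern the questionnaire data, not the reports behind them.

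A reader might also infer three stronger things that the document does not support:

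- **That woredas are rewarded for higher reported utilisation.** Section 2.8.4 does say "Woredas with better performance have been appreciated and recognized". But the parameters listed in the same item are process counts: team meetings, problems identified and prioritised, action plans, and monitoring activities. Service percentages are not among them.
- **That DIPH demonstrably inflates the figures.** Neither the size nor the direction is established.
- **That facility reports are already in hand for a restricted analysis.** Section 2.8.2 mentions data acquired from the six DIPH and six control district offices. No section says that facility-level reports are collected.

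**Conclusion.** The point holds as a limit on what the trial can conclude. Section 2.9 fixes the outcome as a provider-side report, the reporting staff are trained and supported in one arm only, and the section 2.12 estimator removes only change shared by both arms. Any reporting change confined to the DIPH arm would therefore be read as a change in utilisation.

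That such a change occurs is plausible, not shown. The +5 to +7.5 points rest on assumed completeness, flat true utilisation of 50%, an unchanged control arm and unaffected denominators. Other assumed values give more or less, and the bias could be negative. The reasoning applies whether the report is the routine HMIS return or the manager's interview answer. The point matters for the conclusion and is cheap to address; it does not invalidate the design.

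**What to change.** 1. In sections 1.1, 2.9 and 2.12, name the outcome and the conclusion as reported utilisation.
2. In section 2.12, tabulate report completeness by arm at baseline and end line beside the utilisation result, from the data of the 12 district offices. Use the same indicator and denominator rules in both arms.
3. State that no gain in actual utilisation will be claimed if completeness diverges between arms. Similar completeness rules out one explanation only, because recording within facilities may still have changed.
4. If facility-level reports can be obtained, an analysis restricted to facilities reporting in both windows may be added as a sensitivity check and no more. It misses reporting changes within facilities, and it selects on reporting after randomisation, which the intervention may itself affect.

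The cost is a narrower claim and one small extra tabulation. Item 2 assumes that the figures can be traced to routine reports whose completeness can be counted. If they are interview answers only, the wording in item 1 is what remains.
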